### Sample size determination

For the power calculation, mean differences between the treatment group and the placebo group were obtained from Ishizuka et al. [15], who reported that, for constipated subjects, the mean frequency of bowel movements per week was 3.8 at baseline, 4.4 in the second week for those on placebo, and 5.1 in the second week for those on treatment. Data were simulated for each of the two experimental designs for 10,000 subjects assuming correlated Poisson random variables with mean weekly bowel movements as given above. Either the weekly totals as simulated or the averages of the weekly totals for each period (baseline, intervention) were used in subsequent analyses. For the simulations, all washouts were assumed to have the same mean as the placebo (4.4 bowel movements/week) and no temporal trend within each intervention or washout period was assumed. A correlation of 0.35 for the repeated observations on a subject was assumed. This value was obtained from previous studies involving measurement of weekly total bowel movements such as that of Baird et al. [16]. All power analyses were based on using a type I error rate of 0.05 and no correction for possible multiple comparisons. A cross-over study with five time periods, i.e., 4 weeks of baseline, 4 weeks on one treatment, 4 weeks of washout, 4 weeks on the alternative treatment, and 4 weeks post-treatment, was considered. Within each time period, the weekly totals to obtain an average total within each period for each subject were averaged. Hence, the value for any time period for a subject is the mean of the 4 weekly totals. Hypothesis testing included the F-tests in the ANOVA table for ‘Period’ and a *t* test of the difference between the product and placebo. The recommended sample size for this model is 26 to determine a difference between treatments. If the weekly means and then the treatment differences by averaging the least squares means are tested after analysis, the same sample size is required, confirming the appropriate sample size of 26. A washout of 4 weeks is expected to be sufficient to minimize any carryover effects. However, with a possibly high dropout rate of approximately 25% (due to the length of the study), a sample size of 36 is targeted. The targeted sample size is feasible as recruitment will be from a population that includes individuals participating in residential programming and those residing in the community at large.

### Statistical analysis

For the primary outcome of stool frequency, data will be analyzed using a general linear mixed model with intervention, week, period, sequence, and the interactions of period, sequence and intervention with week (weekly data), as the main fixed effects. A random effect of subject will be included in the models. Pairwise tests and post-hoc analyses will be conducted using the Tukey–Kramer method. Kenward–Roger adjustments for the denominator degrees of freedom will be performed to adjust for bias in the covariance estimates for the random effect.

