Constipation is a common problem for individuals with PWS. A study of adults with PWS showed that 40% of these individuals have constipation symptoms, including having less than three defecations per week, sensation of anorectal obstruction, straining during defecation, and having hard stools [4]. Although adequate dietary fiber may be achievable in children with PWS [5], this may be a challenge in adults with PWS, particularly given their low energy needs and, thus, limited food choices. Certain probiotics, “*live microorganisms that when administered in adequate amounts confer a health benefit to the host*” [6], have been shown to improve constipation symptoms in otherwise healthy adults. Probiotics have been shown to significantly decrease transit time, increase stool frequency, and improve stool consistency, particularly *Bifidobacterium lactis* strains [7]. This study will build on previous literature reporting on the efficacy of probiotics in adults with constipation and will examine the effect of *Bifidobacterium animalis* ssp. *lactis* B94 (*B. lactis* B94) in adults with PWS. The aim of the study is to determine the effect of *B. lactis* B94 on stool frequency, stool form (a proxy for transit time), gastrointestinal (GI) symptoms, and fecal microbiota in adults with PWS. It is hypothesized that *B. lactis* B94 will increase stool frequency, decrease the percentage of slow transit stools, and improve GI symptoms. The primary outcome of the study is weekly stool frequency (difference between treatments), whereas secondary outcomes are weekly stool frequency (percentage change from baseline), stool form (percentage change in slow transit Bristol Stool Form Scale (BSFS) 1 and 2 [8] from baseline and between treatments), GI symptoms, and compliance (recorded intake of the provided and remaining supplements).

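### As written, the primary weekly-data model has no subject-by-period term, so the treatment standard error will be too small if weekly stool counts cluster within periods

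*Protocol article*

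**What the plan says.** The Background section names the between-treatment difference in weekly stool frequency as the primary outcome. Under Design, each subject takes one treatment for a single 4-week period and the other for another, within a five-period, 20-week schedule.

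The Statistical analysis section specifies a general linear mixed model for this outcome. Its fixed effects are intervention, week, period, sequence and "the interactions of period, sequence and intervention with week (weekly data), as the main fixed effects". The random part is one sentence: "A random effect of subject will be included in the models". Kenward–Roger degrees of freedom are to be used "to adjust for bias in the covariance estimates for the random effect", in the singular. No subject-by-period effect and no residual covariance among weeks is stated.

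The Sample size determination section simulates correlated Poisson weekly counts with one correlation: "A correlation of 0.35 for the repeated observations on a subject was assumed". It averages the four weekly totals per period and arrives at 26. It then reports that for an analysis of weekly means "the same sample size is required, confirming the appropriate sample size of 26".

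**The concern.** Treatment is randomised to subject-periods, not to weeks. The error that belongs to the treatment contrast is therefore the variation of a subject's period means about that subject's own level. A model with a random subject effect alone forces two weeks in the same month to be exactly as correlated as two weeks in different periods. Anything that shifts a subject for a whole period, such as diet, illness or a change in usual care, goes into the weekly residual. There it is averaged over four weeks as if it were week-to-week noise.

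The protocol gives reasons to expect such shifts. It records diet afresh in every period and leaves usual clinical care running. Its limitations paragraph says that response may differ between constipated and non-constipated participants. With one period per treatment, variable response appears as subject-by-period variation.

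If that variation exists, the primary confidence interval is too narrow and the 5% error rate is not held. Kenward–Roger corrects small-sample inference under the covariance that was specified. It cannot supply a variance component that was left out.

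**Working it through.** **Inputs from the Sample size determination section.** The weekly means are "4.4 in the second week for those on placebo, and 5.1 in the second week for those on treatment", so the difference is 5.1 − 4.4 = 0.7. Poisson variance equals the mean, so the average is (4.4 + 5.1)/2 = 4.75. There are four weeks per period, correlation 0.35 and alpha 0.05.

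**Assumed, because not stated.** A two-sided test, 80% power, and any split of 0.35 into a within-period value rw and a between-period value rb.

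**Step 1: reproduce 26.** With one common correlation, the variance of a subject's difference between two 4-week means is 2 × 4.75 × (1 − 0.35)/4 = 1.544. Then n = 1.544 × (1.960 + 0.842)²/0.7² = 24.7, that is 25 by the normal formula, or 27 by noncentral t. Power at 26 is 0.82 (normal) or 0.79 (t). At 90% power n would be 34 to 36, so 26 fits 80%. For dropout, 26/0.75 = 34.7, so 35, against the 36 targeted.

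**Step 2: true error against model error.** Per unit weekly variance:
- The contrast's true error is A = (1 − rw) + 4(rw − rb), and the variance of a subject's difference is 2 × 4.75 × A/4 = 2.375A.
- The subject-only model replaces A by a pooled residual M, which mixes between-period error (A) with within-period error (1 − rw).
- With 26 subjects in two sequences and two periods modelled, M = [24A + 144(1 − rw)]/168.
- With five periods modelled, M = [96A + 360(1 − rw)]/456.
- Two-sided type I error is 2[1 − Φ(1.96/√(A/M))].

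Example, rw = 0.40 and rb = 0.35: A = 0.60 + 4 × 0.05 = 0.80. With two periods, M = (19.2 + 86.4)/168 = 0.629, A/M = 1.27, and the error is 8.2%.

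| rw (rb = 0.35) | A | A/M, two periods | Type I | A/M, five periods | Type I | Power at 26, valid error term |
|---|---|---|---|---|---|---|
| 0.35 | 0.65 | 1.00 | 5.0% | 1.00 | 5.0% | 0.79 |
| 0.40 | 0.80 | 1.27 | 8.2% | 1.25 | 7.9% | 0.70 |
| 0.45 | 0.95 | 1.56 | 11.7% | 1.50 | 10.9% | 0.63 |
| 0.50 | 1.10 | 1.88 | 15.3% | 1.76 | 13.9% | 0.56 |

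Using the t cut-off on 168 df instead of 1.96 gives 8.0%, 11.5% and 15.0% for two periods. In standard errors at rw = 0.40 with five periods, the model reports 0.242 where the true value is 0.270.

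**Step 3: simulation.** With 4,000 replicates, 26 subjects and five periods, the subject-only weekly model rejected a true null in 4.9%, 8.1% and 10.5% of runs at rw = 0.35, 0.40 and 0.45. The period-mean test rejected in 4.3%, 5.1% and 4.9%. With 36 subjects the weekly model gave 4.9%, 7.8% and 11.2%, so a larger sample does not help.

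**Step 4: other assumed splits (five periods).** If 0.35 is the within-period value and rb is 0.25 or 0.15, the error is 10% or 14%. Serial correlation between adjacent weeks of 0.2 or 0.4 gives about 9% or 16% by simulation.

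**The case against.** Four points carry weight.

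- **The only correlation in the protocol makes the model right.** With 0.35 for every pair of weeks, the standard error is exact and the error is 5%. A reader might infer that the standard error is too small as a matter of fact. The document does not support that: every inflated figure above rests on an assumed split. This stands, and the point is conditional.
- **That subject is the only random term is inferred.** The article says a subject effect will be included and is silent on residual covariance. A suitable structure could sit in the full protocol or the analysis plan, which are not shown, without contradicting the article. This stands as a limit. However, the article does set out the random part for the primary outcome and speaks of one random effect, so the point concerns what is stated.
- **A period-mean model may also be intended.** The text speaks of models in the plural and attaches the weekly-data tag to the interaction terms. With period means, a random subject effect would already give the right error. This is possible, but the section does not name such a model as primary.
- **The two-sided rates overstate false claims of benefit.** By symmetry about half the errors favour the probiotic: roughly 4%, 6% and 8% across the assumed range, against a nominal 2.5%. This is correct, and it is still inflation.

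A reader might also infer that 26 is wrong, or that the sentence on the weekly analysis is false. Neither follows. The figure reproduces, and the two analyses do agree under the simulated conditions. Because those conditions contain one common correlation, the agreement says nothing about clustering within periods.

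**Conclusion.** The concern holds in conditional form. As the article describes it, the primary weekly model protects the 5% error only if weeks in the same period are no more alike than weeks in different periods. Nothing in the protocol supports that equality beyond the single assumed 0.35. For within-period correlation 0.05 to 0.15 above a between-period value of 0.35, with 26 subjects, two-sided type I error is about 8–15% with two periods modelled and 8–14% with five. If the excess is zero, nothing is lost. The size of any excess is unknown from the documents. This is therefore a risk worth removing before unblinding, not a demonstrated error, and it does not by itself contradict 26 or 36.

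**What to change.** Add a random subject-by-period effect to the weekly model, or state a within-subject covariance with separate within-period and between-period correlations. Alternatively, make the period-adjusted comparison of each subject's 4-week means the primary test. If the full protocol or analysis plan already holds such a structure, say so in one sentence. Settle this before unblinding, so that the error term is not chosen after seeing results.

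Keep the statement on 26, with a note that both the figure and its agreement with the weekly analysis hold under one common correlation.

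The change is one model term and needs no new data. The cost is power if the component is real: at 26 subjects it drops from about 0.79 to 0.70, 0.63 or 0.56 for within-period correlations of 0.40, 0.45 or 0.50. By noncentral t, 80% power would then need 33, 39 or 44 subjects instead of 27. That loss is not slight at the upper end, but it reflects the information the design actually carries.

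### The primary B94-versus-placebo contrast is sized as an unadjusted 5% t test, but the analysis section puts pairwise tests under Tukey–Kramer without exempting it; power is lost only if the Tukey family has more than two levels

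*Protocol article*

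**What the plan says.** The Background of the Protocol article names one primary outcome: weekly stool frequency, as the difference between treatments.

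Sample size determination bases the sizing on a t "test of the difference between the product and placebo", alongside F-tests for period, in a crossover with five four-week periods. It adds: "All power analyses were based on using a type I error rate of 0.05 and no correction for possible multiple comparisons". The result is 26 subjects, raised to 36 for dropout of about 25%.

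Statistical analysis specifies, for the same primary outcome, a mixed model with fixed effects for intervention, week, period and sequence, the interactions of period, sequence and intervention with week, and a random subject effect. It continues: "Pairwise tests and post-hoc analyses will be conducted using the Tukey–Kramer method". It does not give the number of levels of intervention or period, does not say whether baseline and washout weeks enter the model, and does not set the primary contrast apart.

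**The concern.** B94 versus placebo is a pairwise test, and the sentence covers pairwise tests as well as post-hoc analyses. Read literally, the primary contrast is adjusted, although it was sized without adjustment.

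Stool data are recorded daily through baseline, both interventions and both washouts, and the only model described for sizing has all five periods. An analyst could therefore give intervention a baseline, washout or no-product level. The primary contrast would then be tested against a critical value that also protects comparisons such as B94 versus washout, which are not the trial's primary question. A single prespecified primary contrast needs no such protection. The adjustment would carry no risk to the type I error rate; its only effect would be a greater chance of missing a real effect in a population that the Discussion itself calls limited.

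**Working it through.** **Inputs, all from Sample size determination**
- Weekly means: "3.8 at baseline, 4.4 in the second week for those on placebo, and 5.1 in the second week for those on treatment". The treatment difference is 5.1 − 4.4 = 0.7.
- Distribution: "assuming correlated Poisson random variables with mean weekly bowel movements as given above". Variance equals the mean; for the two treatment periods it averages (4.4 + 5.1)/2 = 4.75.
- "A correlation of 0.35 for the repeated observations on a subject was assumed".
- Unit of analysis: "the value for any time period for a subject is the mean of the 4 weekly totals".
- Assumed, because not stated: two-sided test, 80% target power.

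**Step 1. Reproduce the 26**
- SD of the within-subject difference = √[2 × 4.75 × (1 − 0.35)/4] = √1.544 = 1.242.
- Standardized effect = 0.7/1.242 = 0.563.
- A five-period ANOVA has 4(n − 1) error df, so 100 df at n = 26.
- Noncentrality = 0.563 × √26 = 2.87; critical t = 1.984; power = 81.2%.
- The smallest n reaching 80% is 26. With n − 1 df it is 27, and by the normal approximation 25. The article's figure is reproduced.

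**Step 2. Same contrast under Tukey–Kramer**

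The critical value is q(0.95; k, df)/√2 for k levels. The noncentrality is unchanged.

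| Levels k | Critical value (100 df) | Power, 26 completers | Loss (points) | Completers for 80% | Power, 36 completers (140 df) |
|---|---|---|---|---|---|
| 2 | 1.984 | 81.2% | 0 | 26 | 91.9% |
| 3 | 2.379 | 68.9% | 12.3 | 33 | 84.3% |
| 4 | 2.613 | 60.3% | 20.9 | 38 | 78.1% |
| 5 | 2.778 | 54.0% | 27.2 | 41 | 73.0% |

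Sensitivity at 26 completers, for three to five levels:
- With n − 1 = 25 df, the losses are 13.9 to 30.1 points.
- With the variance set at 4.4 or 5.1 and 100 df, they run from about 11 to 28 points.
- Simulated correlated Poisson data (4,000 runs, two correlation structures) gave about 82–83% unadjusted, 71% with three levels and 57% with five.

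**Step 3. Which families can the written model form?**
- Period with five levels: B94 and placebo occur only in periods 2 and 4; baseline and washouts occur only in periods 1, 3 and 5. Any pair setting a capsule against baseline or washout is aliased with period. B94 minus placebo is the only estimable intervention contrast.
- Only the two treatment periods analyzed: intervention has two levels, and Tukey–Kramer is the t test.
- Each crossover period coded as a treatment plus its following washout: all three pairs among B94, placebo and washout are estimable, so a three-level family can arise with period still in the model.
- A full four- or five-level family: this needs the period effect dropped or recoded.

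**The case against.** The strongest reply is that the feared families mostly cannot arise. Period is a fixed effect in the model. If it has five levels, no pair involving baseline or washout is estimable; if it means the two treatment periods, intervention has two levels. The article's own usage also favors two: it speaks of intervention periods as distinct from baseline and washout, and subjects take either B94 or placebo. In addition, the sizing section already names the product-versus-placebo test and, for weekly data, treatment differences from averaged least squares means. Tukey–Kramer may therefore have been meant only for follow-up comparisons, and defining its family is usually work for the statistical analysis plan.

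Much of this stands. The estimability argument is correct for a five-level period effect, and a two-level factor costs nothing. But those two codings are not exhaustive: the treatment-plus-washout coding yields three estimable pairs. The omission of a family definition is not the point either. The article itself states an adjustment for pairwise tests and a sample size calculated without one, and does not say which governs the primary contrast.

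Two stronger readings are tempting:
- A reader might infer that Tukey–Kramer definitely costs the trial 12 to 27 points of power. The documents do not support that, because they do not fix the number of levels; the range starts at zero.
- A reader might extend the family to the eight intervention-by-week means. The four-week average difference is not a pairwise difference among those means, so an eight-mean critical value does not apply to it.

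**Conclusion.** The point holds in a conditional form. As written, the primary contrast is sized without adjustment and is not exempted from Tukey–Kramer. The cost is nil with two intervention levels, about 12 points with three (81% to 69%), and about 21 or 27 points with four or five (60% or 54%); the last two apply only if the period effect is dropped or recoded.

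These figures rest on the article's own means, Poisson variance and correlation, 26 completers, and an assumed 80% target with a two-sided test. They shrink if more subjects complete: with all 36, power is 84% at three levels and 73% at five. At the dropout the plan expects, 36 × 0.75 = 27 completers, so the figures for 26 are the relevant ones. This is a wording defect that could cost power; it does not show that the trial is underpowered.

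**What to change.** State in Statistical analysis that the primary test is the single B94-minus-placebo contrast from the mixed model, averaged over the four treatment weeks, at two-sided 0.05 without multiplicity adjustment. Confine Tukey–Kramer to the remaining pairwise and post-hoc comparisons: individual weeks, baseline and washouts.

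The cost is one sentence, settled before unblinding. It changes neither the sample size nor the data collected, and it makes the planned primary test the one that was sized. If the sponsor does intend Tukey–Kramer for the primary contrast with more than two levels, the sample size should be recalculated on that basis: 33, 38 or 41 completers for three, four or five levels, under the same assumptions.

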### Data management

Data and files will be secured in locked cabinets and office space. Paper questionnaires will only include date and assigned participant number. Data that is originally captured as hardcopy/paper (e.g., questionnaires, etc.) will be transcribed to encrypted electronic files. Following the completion of the study, identifiers will be removed from all data.

## Discussion

In this paper, we present a clinical trial design to evaluate the effects of the probiotic *B. lactis* B94 in adults with PWS. *B. lactis* B94 may increase stool frequency, decrease the percentage of slow transit stools, and improve GI symptoms. When consuming the probiotic, subjects may experience improved bowel habits.

This study has limitations. The sample size was determined based on a study of constipated adults as no known published research has explored *B. lactis* administration in PWS subjects. As PWS is a unique patient population, their response to *B. lactis* may differ from those without such a diagnosis. A differing response is possible due to potential disease-specific changes in GI function in individuals with PWS or dissimilarities in dietary intake as individuals with PWS are commonly prescribed energy-restricted diets [3], both of which may impact baseline microbiota and response to *B. lactis*. In addition, bowel habits of individuals with PWS residing in a residential home environment may differ from adults living independently. Furthermore, given the limited population to sample, we are recruiting individuals with PWS independent of constipation status and thus, non-constipated participants may differ in their response to *B. lactis*.

To our knowledge, this is the first randomized, controlled trial evaluating the effectiveness of a *B. lactis* strain on GI wellness in adults with PWS. The results of this study will provide information on the efficacy of *B. lactis* B94 in populations at risk for slow transit and constipation. In addition to pursing publication of the findings of this trial, the authors plan to communicate the results to the study participants and healthcare professionals involved in the care of individuals with PWS.

## Trial status

The current protocol (IRB201701976, version 3) was approved December 4, 2017. Study recruitment began December 2017 and is expected to be completed by December 2018.

